**Figure 2 figure2:**
[figure not shown]
The main menu of CT-MICART features. CT-MICART: Culturally Tailored-Mobile Integrated Cannabis and Anxiety Reduction Treatment.

All participants are also asked to complete a 6-week postrandomization assessment and a qualitative interview. Specifically, at the end of the 6-week EMA period, the follow-up assessment becomes available on the app home screen and takes approximately 30 minutes to complete. The qualitative interview is scheduled with a trained research staff member and focuses on the participant’s experiences using the CT-MICART+EMA or EMA-only app features. Participants can earn up to US $160 in Amazon electronic gift cards for their participation. Specifically, eligible participants are compensated with a US $20 gift card for completing the baseline assessment and a US $50 gift card for completing the 6-week follow-up, including the qualitative interview. Ineligible participants are not being compensated for completing the brief baseline Zoom call. In addition to baseline and follow-up compensation, participants are compensated for their EMA completion based on their completion rate. Those who complete 50% to 70% of all EMA assessments during the 6-week study period will receive a US $30 gift card, those who complete 71% to 79% will receive a US $60 gift card, and those who complete 80% or more will receive a US $90 gift card. Thus, if a participant completes 80% or more of the assessment across the entire 6-week trial, they can earn up to US $160 in electronic gift cards across all assessments.

### Intervention Conditions

#### Overview

All participants have access to a “Call Staff” button that enables participants to easily call the study team. In addition, all participants have access to an “App Instructions” button that provides detailed descriptions of each of the app functions. Finally, all participants are informed that they can click the “Payment” button to view an up-to-the-moment accounting of all EMAs prompted and completed and the current compensation based on EMA and assessment completion.

All participants are instructed to complete all smartphone assessments through Insight (TSET Health Promotion Research Center), an encrypted mobile app through which participants receive all study content. Encrypted data will be automatically password protected and saved to the University of Houston’s and the University of Oklahoma Health Science Center’s institutional server and will only be accessible to the IRB-approved research team members. Moreover, participants are informed during the consent process that they are responsible for any phone service costs related to the study.

#### Active Condition (CT-MICART+EMAs)

##### Overview

The CT-MICART+EMA condition consists of access to the CT-MICART content in the Insight app and 3 prompted daily EMAs. The morning EMA is delivered 30 minutes after the preset waking time, the lunch EMA is delivered at 12:15 PM, and the evening EMA is delivered 1 hour and 15 minutes before the participant’s preset sleep time. The core components of the CT-MICART condition include FSB elimination training and CBT for CUD with culturally tailored content. The CT-MICART+EMA content includes (1) treatment on a “schedule” that is culturally adapted (ie, 12 different 3- to 5-minute treatment video files); (2) participant-driven, automated, individually tailored treatment messages (eg, tailored to each participant’s daily goal of reducing cannabis use, abstaining from cannabis, or no daily goal); (3) “on demand” features (ie, Coping Toolkit and Help Me Reach My Goal); and (4) end-of-day FSB elimination training exercises.

##### Process to Culturally Adapt Treatment

We followed the Cultural Adaptation Process [38] model of treatment adaption to culturally tailor CT-MICART. All treatment videos include depictions of Black adults and accompanying audio is voiced by Black voice actors who worked closely with our research team. Moreover, all app content was reviewed by a diverse Community Research Advisory Board (CRAB) at the Health Research Institute at the University of Houston. The CRAB was consulted: they provided feedback during the app development process, and appropriate modifications were made based on their feedback.

##### Treatment on a Schedule

To provide automated intervention content that is tailored to each participant’s current goals and delivered in a manner that is best matched to their schedule, the app asks participants if they would like to watch 1 of the 12 different 3- to 5-minute treatment videos (ie, 2 videos per week) over the 6-week intervention period. Scheduled video sessions are cued (ie, the phone rings and vibrates) at the scheduled time and every 15 minutes (up to 2 times) after the scheduled time until the participant acknowledges the cue. Participants have the option to delay or reschedule videos or watch them after the scheduled day or time (ie, the next unwatched video populates [in order] in the app after the previous video is viewed). Videos can be watched as many times as desired. The phone records the date or time when each video is watched (ie, both initiation and completion). The 12 brief (3-5 minutes) CT-MICART videos provide psychoeducation on (1) the nature of cannabis use and negative affect (eg, anxiety and stress) and the FSB model; (2) the emotional processing model of negative affect (and how it relates to cannabis) and cannabis-related coping strategies (eg, avoiding people, places, and things); (3) relations between FSB and racial discrimination, negative affect, and cannabis use; (4) cannabis (and other substance) use as an FSB and understanding cannabis use patterns; (5) countering phobias (ie, exposure to anxiety- and stress-provoking stimuli without engagement in FSB, including cannabis) and coping with cravings; (6) fading other FSBs (eg, checking, reassurance seeking, companions, and avoidance of bodily sensations) and managing thoughts related to cannabis use; (7) fading other FSBs (avoidance) and managing negative moods; (8) fading other FSBs (cognitive avoidance) and seemingly irrelevant decisions; (9) problem-solving; (10) managing social influences (refusal skills and assertiveness); (11) planning for emergencies and coping with lapse; and (12) preventing relapse.

##### Tailored and Real-Time Treatment Messages

Participants receive personally tailored messages that are based upon each day’s cannabis cessation or reduction goal (ie, reduce cannabis use today, abstinent from cannabis today, or no cannabis use goal today). Thus, the app “meets participants where they are” and provides messages that is in line with their current goal. On days when the participant has no goal to reduce or abstain from cannabis, the app offers primarily “gain-framed” messages that aim to increase motivation for cannabis cessation or reduction. Importantly, the type of message that is delivered at the end of each EMA is recorded in the database so we may analyze the effect of messages on currently present cannabis use triggers.

##### On-Demand Features

Hundreds of unique messages were developed for this study to address various use risk triggers and to reduce repetition. Messages are consistent with MET-CBT approaches (including ICART) [31] and address identified cannabis use triggers. On-demand content is available through 2 buttons on the app home screen. First, the Coping Toolkit feature contains a menu of resources that become available once this button is pressed (see Figure 3), including Ways to Cope with Urges; Challenge Unhelpful Thoughts (see Figure 4 for a list of automatic thoughts that can be challenged via the app); I’ve Slipped, Now What?; How to Cope with Stress; Coping with Discrimination; Coping with others Using Marijuana; Motivate Me to Stay on Track; and Eliminate False Safety Behaviors (see Figure 5 for menu options). Second, the Help me Reach my Goal feature contains a menu of resources that also become available once this button is pressed (see Figure 6), including Benefits of Reducing or Quitting; Harms of Marijuana Use; Relaxation Exercises; Give Me Something to Do; and I’m Bored, Distract Me. Finally, all participants are instructed to click the “Record Stress or Urge,” “I’m About to Use,” and “I Just Used” buttons (see Figure 2) when appropriate. CT-MICART+EMA participants receive a tailored intervention message at the completion of each participant initiated EMAs.

**Figure 3 figure3:**
[figure not shown]
Coping toolkit CT-MICART feature. CT-MICART: Culturally Tailored-Mobile Integrated Cannabis and Anxiety Reduction Treatment.

**Figure 4 figure4:**
[figure not shown]
Challenging unhelpful thoughts CT-MICART feature. CT-MICART: Culturally Tailored-Mobile Integrated Cannabis and Anxiety Reduction Treatment.

**Figure 5 figure5:**
[figure not shown]
False safety behavior elimination CT-MICART feature. CT-MICART: Culturally Tailored-Mobile Integrated Cannabis and Anxiety Reduction Treatment.

**Figure 6 figure6:**
[figure not shown]
Help me reach my Goal CT-MICART feature. CT-MICART: Culturally Tailored-Mobile Integrated Cannabis and Anxiety Reduction Treatment.

#### Control Condition (EMAs Only)

Participants randomized to EMA only condition receive the baseline, follow-up, qualitative interview, 3 prompted daily EMAs for 6 weeks, and they have access to the participant-initiated “Record Stress or Urge,” “I’m About to Use,” and “I Just Used” buttons. However, they do not receive tailored messages or access to the CT-MICART intervention content.

### Assessments

#### Overview

See Table 1 for a schedule of data collection and measures list. All measures have been used among samples of Black adults.

**Table 1 table1:** Measures and schedule for data collection.

Measure name	Screener	Baseline	6-week follow-up	EMA^a^ items
Demographics or background information	✓			Cannabis use assessment (outcomes)
Motivation to quit cannabis (eligibility)	✓			Alcohol consumption
REALM-SF^b^ (eligibility)	✓			Motivation regarding cannabis use
CUDIT-R^c^ (eligibility)	✓		✓	Watch treatment videos (CT-MICART^d^ condition only)
Legal mandate status (eligibility)	✓			Cannabis use goal assessment (CT-MICART condition only)
Report of cannabis use to manage anxiety or stress in the past month (eligibility)	✓			Negative affect
Assessment of ongoing substance use treatment or anxiety and depression (eligibility)	✓			Confidence in reducing or quitting
Safety Aid Scale (outcome)		✓	✓	Urges or cravings
Qualitative interview (outcome)			✓	Social support and daily interactions
System Usability Scale (outcome)			✓	Coping motives for cannabis and consequences or benefits of using
Credibility or Expectancy questionnaire (outcome)		✓	✓	False safety behavior elimination engagement
Marijuana Motives Measure (outcome)		✓	✓	N/A^e^

^a^EMA: ecological momentary assessment.

^b^REALM-SF: Rapid Estimate of Adult Literacy in Medicine-Short Form.

^c^CUDIT-R: Cannabis Use Disorder Identification Test.

^d^CT-MICART: Culturally Tailored-Mobile Integrated Cannabis and Anxiety Reduction Treatment.

^e^N/A: not applicable.

#### Study Screening and Demographics Questionnaire

All participants are asked to answer questions related demographic characteristics during the Qualtrics screener (eg, race, ethnicity, age, sex, education, and marital status). In addition, participants answer questions related to previous substance use, discrimination experiences, acculturation, anxiety, depression, motivation to quit or reduce cannabis use (ie, “On a scale from 1 to 10 with 1 being ‘not at all motivated’ and 10 being ‘extremely motivated’ how motivated are you to reduce your marijuana use in the next month?”), legal status to engage in substance use treatment, use of cannabis in the past month to cope with anxiety or stress, and ongoing treatment of substance use, anxiety, or depression.

#### REALM-SF Assessment

The REALM-SF is designed to determine if participants have at least a sixth-grade literacy level through a 7-item assessment taken with the help of a research assistant [37]. The REALM-SF is used in this study by the research staff to determine if participants can read the EMA items and intervention content.

#### CUDIT-R Assessment

The CUDIT-R is an 8-item self-report measure designed to identify the likelihood of CUD [35]. The items are rated on a 5-point Likert-type scale where higher scores indicate a higher likelihood of CUD. Scores of 12 or greater indicate probable CUD and it is used as eligibility criteria for this study [35].

#### Safety Aid Scale

The Safety Aid Scale (SAS) is an 80-item measure that is designed to assess FSBs in participants [24]. Examples of items and FSBs include “Avoid being far from home” and “Fiddling with an object (eg, pen).” The items are rated based on how frequently participants endorse the behavior on a scale from 0 (never or rarely) to 4 (almost always). Items are summed to form a total score of FSB use. This measure has demonstrated excellent internal consistency among Black adults [21]. For this study, item reduction analysis was used to reduce the number of items to 22 [39].

#### Marijuana Motives Measure

The Marijuana Motives Measure (MMM) is a 25-item questionnaire that assesses 5 motives for cannabis use including enhancement, coping, social, conformity, and expansion regarding motives for, frequency of, and problems associated with cannabis use [40]. Items are rated on a 5-point Likert-type scale where 1=almost never or never, 2=some of the time, 3=half of the time, 4=most of the time, and 5=almost always or always.

#### System Usability Scale

The System Usability Scale (SUS) is a 10-item questionnaire that is used in this study to evaluate participants’ perceived usability of the app [41]. The SUS includes items related to app engagement, frequency of use, complexity of the app, and thoughts about using the app.

#### Credibility or Expectancy Questionnaire

The Credibility or Expectancy Questionnaire (CEQ) is a 6-item measure that assesses treatment expectancy and rationale credibility [42]. It derives 2 predicted factors including cognitively based credibility and affectively based expectancy. In this study, it is used to gauge participants’ thoughts on the credibility of the intervention and assessment content assigned to them (CT-MICART+EMA or EMA only), and their expectations regarding the intervention (ie, “How successful do you think this intervention will be in helping you quit or reduce marijuana?”).

#### Daily EMAs

Throughout the 6-week intervention period, participants complete 3 daily EMAs occurring at specific times (one 30 minutes after self-selected wake time, one 60 minutes before the self-selected sleep time, and one at 12:15 PM). Items include questions about cannabis use, duration of being high, urges or cravings, motivation, and confidence to reduce or quit cannabis, negative affect, social support, and other substance use. Each EMA also gauges the CT-MICART+EMA participants’ cannabis goal for the day (ie, wanting to avoid using cannabis today, reduce use today, or no cannabis use goal today). All participants are also instructed to access the app’s on-demand assessment features, including the “Record Stress or Urge,” “I’m About to Use,” and “I just used” buttons, when they experience increased stress or an urge to use cannabis as well as anytime they think they might use or after actual cannabis use. Each time participants click these buttons, they are asked to complete a brief set of questions pertaining to their current situation.

#### Qualitative Interview

After completing the 6-week follow-up assessment in the app, study staff are notified via an encrypted email to contact the participant to complete the qualitative interview phone call. Participants are asked to assess their satisfaction with their assigned app content and ways it could be improved via a semistructured interview. This 30-minute interview assesses participant engagement with the app, and specific thoughts about app features including EMA items, intervention content, and why they did or did not use certain features.

### Data Analysis

#### General Overview

Given this pilot study is likely underpowered to detect statistical significance, conclusions will primarily be based on effect sizes and associated Cis, which will be used to guide future, larger, and fully powered trials of comparative efficacy. Prior to data analysis, we will assess the equivalence of groups on key baseline variables. Variables on which the groups differ will be used as covariates in the final analyses.

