### Study Design

A total of 50 Black adults with probable CUD are being recruited through national advertisements across different social media and web-based platforms to participate in this study. Eligible participants are randomized into 1 out of the 2 conditions (ecological momentary assessment [EMA] only vs CT-MICART+EMA). All the participants who consented are asked to complete 3 prompted daily EMAs for 6 weeks. Only participants in the CT-MICART+EMA condition will receive intervention content. Participants are informed during the consent process that they have an equal chance of being assigned to each study condition. Moreover, participants are also informed that one of the study’s treatment conditions consists of watching treatment videos and using CT-MICART app features, while the other condition consists only of completing daily EMAs. Following the 6-week intervention period, all participants will complete a follow-up assessment survey in the app and a qualitative interview phone call. See Figure 1 for the study flow.

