#### Hypothesis Testing

##### Overview

We will examine treatment effects on cannabis use (derived from EMA data) using multilevel models. We will focus on two cannabis use outcomes: (1) use on a given day and (2) frequency of use within a given day. We will account for baseline covariates and time since the start of the intervention. We will also use appropriate random effects and residual constraints. For coping motives for cannabis and FSB engagement, we will conduct a linear regression analysis wherein we will regress treatment condition on each outcome assessed at the 6-week follow-up while adjusting for baseline scores of the specific outcome and baseline covariates. Triangulation mixed methods quantitative or qualitative data analysis [43] will be used to evaluate quantitative and qualitative data.

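### Covariates are chosen by chance baseline differences rather than prognostic value, which costs precision mainly in the two EMA cannabis-use models

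*Protocol article*

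**What the plan says.** Data Analysis, General Overview, sets out a two-step rule. First: "Prior to data analysis, we will assess the equivalence of groups on key baseline variables". Then: "Variables on which the groups differ will be used as covariates in the final analyses". It gives no test, threshold or list of variables. The same paragraph concedes that the pilot is probably underpowered and says that "conclusions will primarily be based on effect sizes and associated Cis".

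Hypothesis Testing, Overview, then describes the models. For the two EMA outcomes (any use on a day, and frequency of use within a day) it says: "We will account for baseline covariates and time since the start of the intervention". No baseline covariate is named there. For coping motives and FSB engagement the regressions are run "while adjusting for baseline scores of the specific outcome and baseline covariates", so one covariate is fixed for each of those outcomes.

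Under Procedures, prompted EMAs begin only after randomisation. Under Participants and in Table 1, CUDIT-R is measured at screening as an eligibility criterion, so every randomised participant should have a score. The screener also asks about previous substance use (Study Screening and Demographics Questionnaire).

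**The concern.** In a randomised comparison, a baseline difference between arms arises by chance. Testing for it answers a question whose answer is already known, and with about 25 per arm a non-significant result does not show equivalence. Adjustment is worth having when a variable predicts the outcome, whether or not the arms happen to differ on it. A rule driven by imbalance therefore tends to discard good predictors and sometimes adds useless ones.

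The EMA cannabis-use models are the exposed ones. They have no pre-randomisation value of the outcome to adjust for, and the only stated route by which a baseline severity measure enters is the difference check. Because the conclusions rest on effect sizes and intervals, interval width is much of what this pilot delivers, and avoidable width is a real loss.

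The binary daily-use outcome raises a further issue. If it is analysed with a logistic model, the conditional odds ratio depends on which covariates are in the model, because odds ratios are non-collapsible. A covariate set decided by chance then also decides which odds ratio is estimated and carried forward to the larger trials.

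**Working it through.** The article gives no power, SD, effect size or interval width, so there is no planned figure to reproduce.

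**Inputs from the article.** N = 50 ("A total of 50 Black adults with probable CUD are being recruited") with equal allocation (participants are told "they have an equal chance of being assigned to each study condition"), so about 25 per arm.

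**Assumptions not in the article.** One baseline predictor with correlation rho to the outcome, rho from 0 to 0.7. The groups differ if p<0.05, or if the absolute standardised difference exceeds 0.2 or 0.1. A single continuous value per participant (SD 1, no treatment effect) stands in for the multilevel models. 20,000 simulated trials per setting.

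**Step 1: what a 5% test can flag.** t(0.975, 48) × √(2/25) = 2.011 × 0.283 = 0.569 SD. Smaller gaps pass as no difference.

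**Step 2: how often a predictor is kept.** Under randomisation a 5% test keeps it in about 5% of trials and omits it in about 95%, however prognostic it is. For a standardised-difference cut-off d, the chance of keeping it is 2 × Φ(−d/0.283):

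- d = 0.2: 2 × Φ(−0.707) = 0.48, so it is omitted in about 52%.
- d = 0.1: 2 × Φ(−0.354) = 0.72, so it is omitted in about 28%.

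**Step 3: mean 95% CI width (SD units) and coverage.**

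| Criterion | rho | Fixed adjustment | Planned rule | Ratio | Coverage of rule |
|---|---|---|---|---|---|
| p<0.05 | 0 | 1.143 | 1.134 | 0.99 | 95.2% |
| p<0.05 | 0.3 | 1.091 | 1.132 | 1.04 | 95.1% |
| p<0.05 | 0.5 | 0.991 | 1.129 | 1.14 | 95.6% |
| p<0.05 | 0.7 | 0.816 | 1.122 | 1.37 | 96.5% |
| Std. diff. >0.2 | 0.3 | 1.092 | 1.118 | 1.02 | 95.5% |
| Std. diff. >0.2 | 0.5 | 0.991 | 1.071 | 1.08 | 96.3% |
| Std. diff. >0.1 | 0.3 | 1.090 | 1.105 | 1.01 | 95.5% |
| Std. diff. >0.1 | 0.5 | 0.990 | 1.033 | 1.04 | 95.5% |

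**Hand check.** Omitting a predictor widens the interval by about 1/√(1 − rho²), less the roughly 1.2% cost of estimating an extra coefficient (at rho = 0, 1.143 with fixed adjustment against 1.130 with none). At rho 0.5: 1/√0.75 = 1.155, and 1.155/1.012 = 1.14, which agrees with the table.

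**Step 4: the regressions with a fixed baseline score.** With the baseline score already in the model (correlation 0.5) and a further predictor adding 0.3, the p<0.05 rule gives 0.991 against 0.940, a ratio of 1.05. With 0.6 and 0.2 it gives 0.917 against 0.897, a ratio of 1.02. These models lose little.

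**The case against.** The strongest reply is that the documents do not support a large effect. Most of it stands.

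- A reader might infer that CUDIT-R is excluded from the EMA models. The article does not say so. It says that variables which differ will be covariates, not that nothing else will be, and the reference to baseline covariates may cover a list kept in a fuller plan. What remains is that the one selection rule actually stated is a poor one, and a fuller plan that followed it would inherit the fault.
- A reader might infer that a strong predictor will usually be dropped. That depends on the missing criterion: a 0.1 standardised-difference cut-off keeps it in about 72% of trials.
- Rho is not in the article. Selecting participants on a CUDIT-R cut-off restricts its range and may lower rho. At 0.3 the loss is 4% or less.
- A reader might infer that the intervals are invalid or that false positives rise. Neither follows. Selection uses baseline data only, coverage is at or slightly above nominal, and the treatment estimate is unbiased over repeated randomisations.
- A reader might infer that the rule changes what every analysis estimates. In a linear model it does not. The point holds only for the binary outcome under a logistic model.
- The trial is a pilot, and Limitations defers efficacy testing to fully powered studies.

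None of this defends imbalance as the reason for choosing a covariate.

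**Conclusion.** The concern holds in a limited form. The stated rule chooses covariates on the wrong ground, and the cost is lost precision, concentrated in the two EMA cannabis-use models. In the settings where the predictor has some value (rho 0.3 to 0.7), intervals run from about 1% wider (rho 0.3, cut-off 0.1) to 37% wider (rho 0.7, p<0.05), with 4% to 14% at rho 0.5 depending on the criterion. Coverage is about 95% to 97%. These figures rest on 25 per arm, an assumed rho, an assumed criterion and a participant-level linear stand-in. They have not been worked out for the multilevel models themselves. For the binary outcome, a logistic analysis would also leave the definition of the odds ratio to chance. This should be fixed because the remedy is nearly free, but it does not threaten the validity of the trial's conclusions.

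**What to change.** Remove the baseline-difference check as a covariate-selection step and report baseline data descriptively by arm. Before arm-level outcomes are seen, fix screener CUDIT-R as a covariate in both EMA cannabis-use models, together with screener cannabis-use frequency if it was recorded. Keep the baseline outcome score in the Safety Aid Scale and Marijuana Motives Measure coping regressions. Any adjustment for variables that happen to be imbalanced can be kept as a labelled sensitivity analysis.

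The cost is a short change to the analysis text and one or two degrees of freedom, with no new data. If CUDIT-R proves unrelated to EMA use, fixed adjustment would widen the interval by only about 1% in the same simulation.
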